### *Intervention Condition*

After obtaining informed consent, a trained community health worker will introduce the DVD to the patient, explaining its purpose and how to use the DVD. Participants will view each intervention DVD installment at their local health center first and then engage in a post-media interview and problem-solving session with a community health worker. After the clinic viewing, the patient will take the DVD home for subsequent review and sharing with family and friends. At three months after randomization, the second installment of the DVD will be delivered for home viewing. After the second viewing, a study visit will be scheduled for a “post-media” interview and re-measurement of BP by a trained community health worker.

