### *Comparison Condition*

Participants randomized to the comparison condition will receive DVDs with only didactic material about common non-communicable diseases (e.g. diabetes, heart disease, chronic lung disease—“Learn More”) but without HTN related stories. Otherwise, the treatment and study assessments for the intervention and comparison groups will be identical. The comparison group will receive usual medical care through the CHC.

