### *Data collection and management*

Data will be collected at the time of baseline trial enrollment and subsequent follow-up visit at the participants' local CHC 3 months after randomization. Each study participants BP will be measured at each study visit according to a standardized protocol developed by the WHO. Trained community health workers will use a calibrated Omron automated monitor

to measure participant's BP, and the average of the last 2 of 3 readings will be entered into the database. Height and weight will be measured in the absence of shoes and heavy clothing while waist and hip size will be measured by placing the tape horizontally around the smallest part of the waist and the widest portion of the hips, respectively. Information on patients' use of traditional medicine for managing their HTN will also be collected..

Trained research nurses at each of the local CHCs will collect data on study participants socio-demographic factors and CVD risk factors including tobacco use, alcohol consumption, salt intake, and physical activity using the WHO STEPS questionnaires, which have been validated and used in previous studies examining risk factors for chronic diseases among rural Vietnamese adults.[28-31] We will ascertain self-reported engagement with the DVDs, including total viewing minutes, specific segments that were viewed, and whether the DVD was shared with family or friends. "Transportation" is a formally validated concept measuring absorption into the video narrative that has been linked to intervention effectiveness.[20, 21] Semi-structured interviews with the intervention group will solicit suggestions for refining the intervention before the larger trial. For example, participants will be asked to elaborate on what motivated or hindered their engagement with the intervention.

Data will be directly entered into a secure, password-protected, internet-enabled, laptop computer. The computer software will have a comprehensive set of built-in quality checks, such as mandatory completion of critical fields and out-of-range flags. After each instrument has been translated, the surveys will be uploaded into REDCap, an Internet-enabled database developed by the NIH Clinical and Translational Science Award program, which was successfully used in our previous work and which is available at no cost.

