### *Study Outcomes*

Feasibility outcomes include recruitment, retention, engagement, and treatment fidelity. Recruitment rates will be calculated from the number of patients approached and reasons for ineligibility and non-participation. We will record the number and reasons for failure to complete the follow-up assessment. Intervention engagement, which will be mainly ascertained from the patient survey as described above, includes time spent watching the

DVD, satisfaction with the viewing experience, and “transportation” into the story line.

Treatment fidelity will be determined by the Vietnam Co-PIs directly monitoring 20% of all study enrollment and follow-up visits and completing a fidelity checklist which will be carefully documented. Exploratory outcomes will include levels of systolic and diastolic BP and the proportion of participants with controlled BP defined as in JNC-8 ( $\leq 140/90$  mmHg for all individuals –a different cut-off will be used for those patients  $\geq 60$  years old and do NOT have diabetes and do NOT have chronic kidney disease for whom BP should be  $\leq 150/90$  mmHg) at three months after randomization.

The recruitment and retention rates of study participants will be calculated for each follow up visit in order to implement the intervention in a timely manner. Given our previous survey data about an individual’s willingness to participate in a clinical trial of HTN conducted at this study site, these rates are anticipated to be greater or equal to 80%. Examination of our final recruitment and retention rates will allow us to focus on specific aspects of the study protocol that need to be revised. Patient’s engagement and treatment fidelity will be collected through a questionnaire survey. Based on patient’s feedback, we will revise the intervention accordingly. We anticipate that changes in BP from baseline enrollment would be 2 mmHg or greater among those in the intervention than in the control group. Based on these findings, we will carry out sample size estimates to have adequate power to detect meaningful between group differences in our pre-specified major trial endpoints.

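### The Intervention Condition section schedules the follow-up BP visit after the second DVD viewing, while other sections fix it at 3 months; if the first rule is followed, follow-up may depend on viewing

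*Protocol*

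**What the plan says.** The protocol (Phase 2) describes the follow-up visit in several places.

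- **Intervention Condition.** On the second DVD: "At three months after randomization, the second installment of the DVD will be delivered for home viewing". Then: "After the second viewing, a study visit will be scheduled for a" post-media interview and a repeat BP measurement. No date, window or fallback is given for someone who does not view it. Earlier in the same paragraph: "Participants will view each intervention DVD installment at their local health center first".
- **Comparison Condition.** Apart from the DVD content, "the treatment and study assessments for the intervention and comparison groups will be identical". No viewing trigger is mentioned.
- **Data collection and management.** Data are collected at baseline and at a "subsequent follow-up visit at the participants' local CHC 3 months after randomization". Viewing is not a condition. Engagement, including minutes viewed, is self-reported.
- **Study Outcomes.** BP level and BP control are exploratory outcomes assessed "at three months after randomization". On retention: "We will record the number and reasons for failure to complete the follow-up assessment". Recruitment and retention are each expected to reach at least 80%.
- **Study Outcomes, closing paragraph.** Staff remind participants one week before the scheduled visit. If the visit is missed, staff interview the participant and measure BP at home within 2 weeks of it. Staff also telephone every 2 weeks about DVD use.

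**The concern.** The protocol contains two rules for when the intervention-arm BP visit is arranged. One is an event, viewing the second DVD. The other is a date, 3 months after randomization. They agree only for a participant who views promptly, and the protocol does not say which prevails.

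The conflict matters most for participants who do not view the second DVD. Under the event rule their follow-up has no trigger, so whether an outcome is collected could depend on adherence to the intervention being tested. These participants are also the most informative ones for a feasibility trial, because their reasons for disengaging are what the investigators need before a larger trial.

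Retention and engagement are two of the four feasibility outcomes listed in Study Outcomes. If a participant who was willing to be measured is lost only because no visit was arranged, a failure of engagement is recorded as a failure of retention. The protocol intends to use its recruitment and retention rates to decide which procedures to revise.

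**Working it through.** The protocol gives no figure to reproduce on this point, so the check is a comparison of sections. It follows one intervention participant who does not view the second DVD under each rule.

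| Step | Intervention Condition rule governs | Data collection rule governs |
|---|---|---|
| Visit arranged? | No trigger stated | Yes, at 3 months |
| Reminder one week before? | No scheduled visit to precede | Yes |
| Home interview and BP if missed? | No scheduled visit to miss | Yes, within 2 weeks |
| BP and survey data | May be absent | Collected, or a genuine non-completion |
| Counted in retention | As not completing, though possibly willing | According to actual completion |

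**Which rule prevails.** The Intervention Condition section is where staff in that arm would look for the sequence of events. The data collection section, the outcome definition and the statement that assessments are identical across arms all point to the dated visit. Nothing ranks one above the other.

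**Timing.** The second DVD is delivered at three months and, under the event rule, the visit follows its viewing. The visit then falls after three months by an unstated interval that depends on the participant. Under the dated rule, the 3-month BP is taken at about the time the second DVD arrives, so with little or no exposure to it. Both statements cannot describe the same visit.

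**Nature of the trigger.** One sentence has each installment viewed at the health center first; another has the second delivered for home viewing. If the home statement applies, the trigger is an unsupervised act that staff learn of only by report.

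**Effect on the retention rate.** The intervention arm has 2 communes × 25 = 50 participants. Each participant left without a visit lowers arm retention by 1/50 = 2 percentage points, and overall retention by 1/100 = 1 point. As an illustration only, 10 such participants would bring the arm to 40/50 = 80%, the bottom of the anticipated range, even if all 50 would have attended a dated visit. The figure of 10 is an assumption; the protocol gives no expected rate of non-viewing.

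**Effect on engagement.** If only those who viewed the second DVD were surveyed, the proportion of respondents who viewed it would be 100% whatever the true proportion. This applies only to that yes/no item. Viewing minutes, satisfaction, transportation and use of the first DVD would still vary among respondents.

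**The case against.** The best defence is that the Intervention Condition wording describes the expected order of events and is not a condition. It does not say that non-viewers are left out. The data collection section gives everyone a dated visit, and the reminder and home measurement then apply to everyone. The fortnightly calls make it unlikely that a participant who stops viewing goes unnoticed. Non-completion is recorded with reasons, and the Data Analysis Plan examines the extent and mechanisms of missing data.

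Much of this stands, and it rules out three stronger readings.

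- *That a non-viewer generates no visit.* A reader might infer this from the Intervention Condition section alone. It holds only if that section overrides the dated visit, which the protocol does not say.
- *That BP, retention and engagement are measured only among viewers.* Non-completers are counted in retention, so it is not restricted to viewers. Low or zero viewing can be recorded at a visit.
- *That the BP bias can be quantified.* With assumed non-viewing of 20% and an assumed BP change 3 to 10 mmHg worse in non-viewers, the measured arm mean would be too favourable by 0.2 × 3 = 0.6 to 0.2 × 10 = 2.0 mmHg, against the anticipated 2 mmHg difference. Neither input is in the protocol. The sum also requires every non-viewer to go unmeasured and no similar selection among comparison participants, who receive DVDs too. If identical assessments meant the same trigger in both arms, some of the bias could cancel. These figures should not be reported as a finding.

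The defence does not remove the conflict. The reminder and home visit both presuppose a scheduled visit, so they protect non-viewers only if the dated rule governs. Recording reasons for non-completion does not recover the missing BP and survey data.

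**Conclusion.** The point holds as an inconsistency with a conditional consequence. The protocol states two incompatible rules for arranging the intervention-arm follow-up visit and does not say which applies. If sites follow the viewing-based rule, participants who do not view the second DVD may have no visit, reminder or home measurement. BP and survey data may then be selectively missing, and retention becomes mixed with engagement. If sites follow the dated rule, this does not happen.

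The only size that follows from the protocol's numbers is 2 percentage points of intervention-arm retention per participant affected. How many would be affected, and any resulting BP bias, cannot be derived. BP is exploratory and the protocol acknowledges limited ability to test effectiveness, so the main stake is the interpretation of retention and engagement. The inconsistency should be corrected, but it does not invalidate the trial.

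**What to change.** Reconcile the Intervention Condition section with Comparison Condition, Data collection and management, and Study Outcomes:

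1. Replace the viewing-based trigger with a follow-up BP and survey visit scheduled by date from randomization, for every enrolled participant in both arms, whether or not a DVD was viewed.
2. At that visit, record whether each DVD was viewed and, if not, why.
3. State that the one-week reminder and the home visit run from that date.
4. Reconcile the delivery of the second DVD at three months with the 3-month outcome, and the health-center-first statement with the home-viewing statement. How these are resolved is for the investigators.

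The cost is one reworded sentence in Intervention Condition, a matching line in the visit schedule, and a short viewing-status item on the follow-up form. Steps 1 to 3 add no visits, since a 3-month follow-up is already planned for all 100 participants.

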### *Comparison Condition*

Participants randomized to the comparison condition will receive DVDs with only didactic material about common non-communicable diseases (e.g. diabetes, heart disease, chronic lung disease—“Learn More”) but without HTN related stories. Otherwise, the treatment and study assessments for the intervention and comparison groups will be identical. The comparison group will receive usual medical care through the CHC.

### *Translation of Survey Instruments*

We recognize the complexity involved in cross-cultural adaptations of behavioral interventions and in translating survey instruments and data collection protocols. In adapting the study protocols and translating the data collection instruments into Vietnamese, we will follow the set of best practices developed by the United States Census Bureau.[26] According to this protocol, translation will be accomplished by a translation team, with multiple versions prepared in parallel followed by team meetings to reconcile differences.

Our translation team will consist of the two Co- Principal Investigators (PI) from Vietnam who are fluent in the language, the PIs in the US, who bring important expertise about HTN and the intervention approach, and an expert in psychometrics. The translation process involves the following iterative steps: prepare, translate, pretest, revise, and document. In the preparation phase, the translation team will be given all relevant material to understand the purpose of the study, the intended audience, and the data collection modality and setting; translation by the Vietnam Co-Principal Investigators will proceed in parallel, with differences reconciled at team meetings. The pretesting phase will consist of cognitive interviews with five participants drawn from the local community. Cognitive testing will identify constructs specific to the Vietnamese language and culture so that appropriate adjustments may be made to ensure cross-cultural equivalence.[27] Several cycles of revision will be accomplished at full committee meetings conducted in person and by Internet video link. Each step in the process will be carefully documented. The ultimate aims of the translation process will be to produce a product that is reliable with semantic equivalence, technical accuracy and textual completeness, reads with fluency with a natural flow in Vietnamese, is appropriate to the literacy level of the intended audience, and is appropriate in style, tone, and degree of formality.

### *Data collection and management*

Data will be collected at the time of baseline trial enrollment and subsequent follow-up visit at the participants' local CHC 3 months after randomization. Each study participants BP will be measured at each study visit according to a standardized protocol developed by the WHO. Trained community health workers will use a calibrated Omron automated monitor

to measure participant's BP, and the average of the last 2 of 3 readings will be entered into the database. Height and weight will be measured in the absence of shoes and heavy clothing while waist and hip size will be measured by placing the tape horizontally around the smallest part of the waist and the widest portion of the hips, respectively. Information on patients' use of traditional medicine for managing their HTN will also be collected..

Trained research nurses at each of the local CHCs will collect data on study participants socio-demographic factors and CVD risk factors including tobacco use, alcohol consumption, salt intake, and physical activity using the WHO STEPS questionnaires, which have been validated and used in previous studies examining risk factors for chronic diseases among rural Vietnamese adults.[28-31] We will ascertain self-reported engagement with the DVDs, including total viewing minutes, specific segments that were viewed, and whether the DVD was shared with family or friends. "Transportation" is a formally validated concept measuring absorption into the video narrative that has been linked to intervention effectiveness.[20, 21] Semi-structured interviews with the intervention group will solicit suggestions for refining the intervention before the larger trial. For example, participants will be asked to elaborate on what motivated or hindered their engagement with the intervention.

Data will be directly entered into a secure, password-protected, internet-enabled, laptop computer. The computer software will have a comprehensive set of built-in quality checks, such as mandatory completion of critical fields and out-of-range flags. After each instrument has been translated, the surveys will be uploaded into REDCap, an Internet-enabled database developed by the NIH Clinical and Translational Science Award program, which was successfully used in our previous work and which is available at no cost.

### *Study Outcomes*

Feasibility outcomes include recruitment, retention, engagement, and treatment fidelity. Recruitment rates will be calculated from the number of patients approached and reasons for ineligibility and non-participation. We will record the number and reasons for failure to complete the follow-up assessment. Intervention engagement, which will be mainly ascertained from the patient survey as described above, includes time spent watching the

DVD, satisfaction with the viewing experience, and “transportation” into the story line.

Treatment fidelity will be determined by the Vietnam Co-PIs directly monitoring 20% of all study enrollment and follow-up visits and completing a fidelity checklist which will be carefully documented. Exploratory outcomes will include levels of systolic and diastolic BP and the proportion of participants with controlled BP defined as in JNC-8 ( $\leq 140/90$  mmHg for all individuals –a different cut-off will be used for those patients  $\geq 60$  years old and do NOT have diabetes and do NOT have chronic kidney disease for whom BP should be  $\leq 150/90$  mmHg) at three months after randomization.

The recruitment and retention rates of study participants will be calculated for each follow up visit in order to implement the intervention in a timely manner. Given our previous survey data about an individual’s willingness to participate in a clinical trial of HTN conducted at this study site, these rates are anticipated to be greater or equal to 80%. Examination of our final recruitment and retention rates will allow us to focus on specific aspects of the study protocol that need to be revised. Patient’s engagement and treatment fidelity will be collected through a questionnaire survey. Based on patient’s feedback, we will revise the intervention accordingly. We anticipate that changes in BP from baseline enrollment would be 2 mmHg or greater among those in the intervention than in the control group. Based on these findings, we will carry out sample size estimates to have adequate power to detect meaningful between group differences in our pre-specified major trial endpoints.

To prevent/minimize losses to follow up and missing data, one week before the scheduled follow-up visit local staff will contact participants by phone as a reminder or by a home visit. Since the communes are small, it is easy to visit participant’s homes. For participants who miss the follow up visits, study staff will come to their homes to interview and measure their BP within 2 weeks of a scheduled follow-up visit. During the course of the study, local staff will call participants every 2 weeks to find out if participants need any technical support for using DVD players, and encourage them to view the standardized DVDs more frequently to improve their adherence to the study intervention. Data collection forms are designed to be relatively short, straight forward, and culturally adapted which will

limit respondent burden and inconvenience. Finally, participants will receive a DVD player at no cost at the beginning of the study and an Omron BP monitor when they finish the study to support their initial and continued participation in the study.

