## **Patient Population**

Individuals 50 years or older with uncontrolled HTN (n = 100) will be assigned to intervention versus comparison status based on the commune in which they reside.

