## *Participant Eligibility*

To be enrolled in this feasibility study, consenting adult men and women must fulfill each of the following criteria: (1) be a resident of the selected commune; (2) be aged 50 years or older; (3) have a diagnosis of HTN according to the 7th Joint National Commission of High Blood Pressure (JNC 7)[9]; (4) have BP measures consistently elevated at 2 time points (screening and 2 week after screening); (5) not be cognitively impaired (as assessed by study physicians); (6) not be a “story teller” who was used to develop the intervention; and (7) not be a family member of another participant in the study. We will restrict our patient population to patients aged 50 years or older since their prevalence of HTN is greatest, they are interested in storytelling, and they face unique challenges to managing their HTN.

Trained study nurses at study sites will explain to eligible persons about the study’ procedures and will obtain informed consent. Patients will be excluded if they are pregnant or unable or unwilling to provide informed consent.

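### Entry and the exploratory BP-control outcome rest on unaligned definitions, so some participants aged 60 or older may already meet the outcome at baseline

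*Protocol*

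**What the plan says.** Three sections of the Protocol bear on this.

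- **Participant Eligibility.** A participant must "be aged 50 years or older", have hypertension diagnosed by JNC 7, and "have BP measures consistently elevated at 2 time points (screening and 2 week after screening"). JNC 7 is attached to the diagnosis criterion. The elevated-BP criterion names no guideline and no mmHg figure. Neither criterion varies with age or comorbidity.
- **Patient Population (Summary).** "Individuals 50 years or older with uncontrolled HTN (n = 100) will be assigned to intervention versus comparison status". Uncontrolled is not defined there.
- **Study Outcomes.** Control at three months after randomization follows JNC-8: ≤140/90 mmHg in general, and a separate limit of ≤150/90 for participants at least 60 "years old and do NOT have diabetes and do NOT have chronic kidney disease for whom BP should be" within it. BP levels and control are labelled exploratory.

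The Data Analysis Plan section compares rates of BP control between the two groups. It mentions no split by baseline control status. Data collection and management lists socio-demographic items and "CVD risk factors including tobacco use, alcohol consumption, salt intake, and physical activity using the WHO STEPS questionnaires". Diabetes and kidney disease are not named in that list.

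**The concern.** An outcome that counts people brought under control is meaningful only for those who start out not controlled by the same rule. Here entry and outcome refer to different guidelines, and only the outcome has an age- and comorbidity-dependent limit. With entry at 140/90, a 65-year-old at 145/85 without diabetes or kidney disease enters as uncontrolled and already satisfies the outcome.

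Three consequences follow for the control rate.

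- It mixes people brought under control with people who were never uncontrolled by its own rule, so it is too high in both arms.
- The between-arm contrast is diluted by participants with little room to improve on this measure.
- With two communes per arm, a chance difference in age or comorbidity mix moves the rate without any intervention effect.

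**Working it through.** The protocol states no control rate and no power calculation, so there is no figure to reproduce. The check compares the two definitions and then sizes the overlap.

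**Step 1: do the regions overlap?** Let L be the systolic entry limit, which is not printed. A participant in the 150/90 subgroup with SBP from L to 150 and DBP ≤90 at the qualifying visits meets both entry and outcome.

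- L below 150: the overlap is a real band. For L = 140 it is 140 to 150 mmHg.
- L = 150: only values exactly on a limit overlap, because the outcome limits include equality.
- Entry strictly above each participant's own outcome limit: no overlap. The protocol does not say this.

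**Step 2: how large is it?** All inputs here are assumptions. Entry needs SBP ≥140 or DBP ≥90 at both time points. In the 150/90 subgroup, mean SBP is 135-145 with between-person SD 18-22, and DBP is 82 with SD 11. Visit-to-visit SD is 8 for SBP and 5 for DBP, and the SBP-DBP correlation is 0 to 0.6. The quantity simulated is

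P(SBP ≤150 and DBP ≤90 at the second visit, given elevated at both visits).

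| Assumption set | Already within 150/90 at second visit |
|---|---|
| As above, readings in whole mmHg | 17-23% |
| As above, readings treated as continuous | 15-20% |
| Mean SBP 130-140, SD 18-20, visit SD 8-10; DBP 80, SD 9 | 24-29% |
| Same as the row above, but entry at 150/90 | 4-6% |

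The value entered in the database is the mean of two readings, so exact ties will be rarer than the whole-mmHg rows imply. A working range for 140/90 entry is 17-24%.

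**Step 3: participants out of 100.** Multiply by the subgroup's share of the sample, assumed to be 40-60%.

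- 140/90 entry: 0.17 × 40 = 6.8 to 0.24 × 60 = 14.4, so about 7-14.
- Widest range from the table: 0.15 × 40 = 6 to 0.29 × 60 = 17.4, so about 6-17.
- 150/90 entry: 0.04 × 40 = 1.6 to 0.06 × 60 = 3.6, so about 2-4.

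**Step 4: effect on the comparison.** Suppose the intervention cannot change the result in those already controlled. The contrast then shrinks by their share, here up to 7-14% of its size.

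For age mix, the first assumption set with a third visit and no treatment effect gives 21-29% within 150/90 and 8-14% within 140/90. Within any one scenario the gap is 12-16 percentage points. If the subgroup were 40% of one arm and 60% of the other, the null control rates would differ by 0.20 × 12 = 2.4 to 0.20 × 16 = 3.2 points.

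**Step 5: what is not due to the mismatch.** Part of the null control rate is regression to the mean. Even among subgroup members above 150/90 at the second visit, 14-21% fall within it at the third. Aligned definitions would not remove that.

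**The case against.** The strongest reply is that the overlap is not printed. JNC 7 qualifies only the diagnosis; the elevated-BP criterion has no cut-off. The one definition of control in the protocol is the outcome's. If uncontrolled is read against it, the 65-year-old at 145/85 is not eligible and the overlap largely disappears. This reading is possible, and it makes the size conditional. It does not remove the point, because no section states it and sites would have to guess.

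Other parts of the reply stand:

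- A reader might infer that people are counted as controlled on the day they enrol. They are not. Control is assessed only at three months; some participants may merely meet the definition at baseline.
- A reader might infer that the trial's conclusions are at risk. The documents do not support that. The aim is feasibility and acceptability, control is exploratory, the same rule applies in both arms, and the protocol concedes limited ability to test effectiveness.
- The planning inputs named for the main trial are chiefly BP change, outcome variability and the ICC. The control rate is not singled out.
- Diabetes and kidney disease cannot be called uncollected. The list of risk factors is introduced as non-exhaustive.
- Equality counting on both sides is minor: about 2-4% under the general ≤140/90 rule, on assumed inputs.
- Splitting by baseline control is ordinary SAP content, and the SAP is not shown. The point rests on the protocol's definitions, not on a missing analysis.

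**Conclusion.** The point holds as a modest one. Entry and outcome are not aligned, and no section requires participants to be uncontrolled by the outcome's rule. For any systolic entry limit below 150, some participants aged 60 or older without diabetes or kidney disease meet the control definition at baseline.

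With 140/90 entry this is roughly 17-24% of that subgroup, or about 7-14 of 100. With 150/90 entry it falls to a few boundary cases. The entry limit, the BP distributions and the subgroup share are all assumptions, so the existence of the overlap under 140/90 is firmer than its size. Only the control rate and its comparison are affected. Recruitment, retention, engagement, fidelity and the continuous BP comparisons are untouched.

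**What to change.** 1. Print the BP limit that defines elevated in Participant Eligibility, and reconcile that section with Patient Population and Study Outcomes. Which clinical limit is right is for the investigators and is not judged here.
2. Classify each participant's baseline control with the Study Outcomes rule, and name the visit whose reading is used.
3. Compare three-month control among those not controlled at baseline by that rule, and show the already-controlled separately by arm.
4. Confirm that diabetes and chronic kidney disease status is recorded at baseline, so that the rule can be applied to every participant aged 60 or older.

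The cost is a few sentences and, if the forms lack them, two baseline questions. Enrolment need not change. The downside is a smaller denominator for the control rate, by about 7-14 of 100 under the assumptions above. If the SAP already makes this split, only the first and fourth items remain.
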